### Exclusion criteria

The participant may not enter the study if any of the following apply:

They are a female participant who is pregnant, lactating or planning pregnancy during the course of the study, they have had recent (<one month) use of inhaled or oral corticosteroids or a recent (<one month) adenotonsillectomy.

Participants will be excluded if they are currently or recently (<14 days) taking antibiotics, there is a clear alternative diagnosis such as pneumonia or they have a known immune deficiency (such as HIV, active chemotherapy or advanced cancer), are scheduled elective surgery or other procedures requiring general anaesthesia during the next seven days, are terminally ill, or have symptoms or signs suggesting that hospital admission is required (such as being completely unable to swallow, very systemically unwell or peritonsillar abscess).

They are also excluded if the patient is judged by the GP to require immediate antibiotics, has a history of severe affective disorders including steroid-induced psychiatric illness, is currently taking any medication on the British National Formulary (BNF) listed contraindications to oral steroids or has existing symptoms that are also side effects of oral steroids or if the patient is taking other interacting medication (for example phenytoin and anti-coagulants). Clinicians are asked to use the BNF and their clinical prescribing systems to check for interactions for all patients.

Further to this patients are excluded if they have a known dexamethasone allergy or if they have any other significant disease or disorder which, in the opinion of the investigator, may either put the participants at risk because of participation in the study, or may influence the result of the study or the participant’s ability to participate in the study.

If the patient has been involved in another clinical trial of an investigational medicinal product in the last 90 days or any other research within the last 30 days, the recruiting primary care site is not the patients usual practice if the patient is not expecting to still be with the primary care site in one month ( temporary residents), they have previously participated in the TOAST trial the patient is unable to be randomized by the end of the (working) day of presentation or they have a requirement for a live vaccine in the next seven days they will also be excluded.

### Expenses and benefits

Healthcare visits in addition to normal care are not anticipated, nor does the trial offer any other payment for involvement in the study, however if additional travel expenses are incurred due to an extra visit to the GP for the baseline trial assessment these expenses will be covered. Trial medication is provided free of charge, but participants will have to pay for their antibiotic prescription, if one is given. However, participants who return a completed symptom diary to the Primary Care Clinical Trials Unit (PC-CTU) are being sent a £10 gift card as a thank you for participating and completing all the follow-up documentation.

### Study procedures

#### Informed consent

The participant must personally sign and date the latest approved version of the informed consent form before any study specific procedures are performed. Written and verbal versions of the participant information sheet and informed consent are presented to participants by the responsible clinician detailing no less than the exact nature of the study, the implications and constraints of the protocol, the known side effects and any risks involved in participation. It is clearly stated that the participant is free to withdraw from the study at any time for any reason without prejudice to future care, and with no obligation to give the reason for withdrawal.

The participant receives the participant information sheet at their initial consultation with their GP, and if eligible and interested, is referred on to a baseline trial assessment with a recruiting clinician for full consent procedures and trial procedures. This gives participants the opportunity to consider the information, and to question the recruiting clinician, their GP or other independent parties to decide whether they will participate in the study. Written informed consent is then obtained by means of participant dated signature and dated signature of the person who presented and obtained the informed consent. The person who obtained the consent must be suitably qualified, experienced and trained in line with the Medicines and Healthcare Products Regulatory Agency, MHRA requirements, and have been authorized to do so by the Chief Investigator. A copy of the signed informed consent will be given to the participants and the original signed form will be retained at the study site.

#### Screening and eligibility assessment

The primary care site gives adults presenting with sore throat a participant information sheet which details what is involved in trial participation. During the initial consultation the primary care clinician (referred to from now onwards as the responsible clinician) discusses trial participation and screens the participant using the inclusion and exclusion criteria. The responsible clinician may be a triage nurse if the GP judges that they are competent to perform the baseline assessment and eligibility screening. Any patient who is not eligible to participate or declines to participate will be recorded on the screening log with reasons for ineligibility or declining (if known) and have no further involvement in the trial.

The responsible clinician completes their routine clinical management, and at the clinician’s discretion will offer a delayed antibiotic prescription, to be collected by the patient either from the recruiting clinician at their subsequent baseline trial assessment, or from the reception of the GP practice according to the standard procedure of the practice. The delayed antibiotic prescription will be accompanied by: reassurance that antibiotics are often not needed immediately and information about the disadvantages of antibiotics, information about the natural history of sore throat and advice to use regular pain relief, instructions for the antibiotics to be collected and used after three to five days if the patient feels their symptoms are not starting to improve, or sooner if their symptoms are getting significantly worse and a brief information leaflet containing instructions and explanation regarding a delayed prescription to reinforce these points.

#### Baseline assessments

Within six hours of the initial consultation, potentially eligible patients undergo a baseline trial assessment with a primary care clinician allocated by the practice to recruit patients (from here on known as the recruiting clinician).

At this meeting a full trial explanation is given and time allowed for the participant to ask any questions, and then written consent is obtained. The recruiting clinician uses a secure, web-based data collection platform (hosted by the University of Oxford) to enter the participant’s baseline data and confirm eligibility using a standard computer within the GP practice. Once the eligibility is confirmed, randomization proceeds.

The recruiting clinician gives the participant standardized instructions regarding how to complete the symptom diary and other response forms and observes the participant taking the trial medication (oral corticosteroid or placebo). The recruiting clinician records the participant’s contact details for the 24- and 48-hour data collection contacts. Those participants for whom the GP has deemed a delayed antibiotic prescription is appropriate are provided with the prescription if this is the standard procedure of the practice.

The recruiting clinician takes a bacterial throat swab. These are being analyzed for streptococcus A, C and G. The participant’s date of birth, sex and the participant trial ID number are being used as identifiers for these swabs. In the rare event that an unusual and potentially dangerous pathogen is detected by bacterial throat swab, and the medically qualified Chief Investigators feel it is appropriate, the practice will be informed of these results.

Baseline case report form data items are:

Socio-demographic factors which will include: age, gender, smoking history and paid work or education. Medications which will include: decision whether or not to offer delayed antibiotic script and if offered, type of dose, dosing regimen and duration of antibiotics prescribed as well as whether the practice left the script for collection at reception or gave it to the patient at the baseline recruitment meeting and any other advised treatment. Symptoms which will include: the duration of sore throat and painful swallowing and the presence or absence of cough, hoarse voice, coryza and fever in last 24 hours, all of which use a validated scale, where ‘None’ is equal to absence of and ‘Slight’ ‘Moderate’ and ‘Severe’ are equal to presence of. Clinical examination findings which will include the confirmation of: the presence of pharyngeal inflammation, the presence of tonsils, the presence of inflamed tonsils, the presence of purulent tonsils, the presence of cervical lymphadenopathy, the presence of tender cervical lymphadenopathy, the participants temperature and type of thermometer used for measuring. Patient-completed items which will include: ratings of throat soreness, pain on swallowing and difficulty swallowing using visual analogue scales, baseline severity ratings using symptom diary and completion of the EuroQol EQ-5D-5L instrument [20].

All these procedures happen according to the schedule of procedures; see Additional file 2.

#### Randomization and codebreaking

Randomization was performed by the Oxford PC-CTU and is stratified by centre (Oxford, Bristol and Southampton) and by receipt or not of delayed antibiotic prescription using a block randomization with variable block size. An independent statistician based in the Department of Primary Care Health Sciences at the University of Oxford generated the randomization schedule. They produced a list of four-digit unique medication IDs; these were printed on the medication labels in variable block sizes stratified as above. This statistician is not involved in any other aspect of the trial.

Each site is initially allocated to hold two sets of two to three packs of pre-randomized medication, one set for those who are given an antibiotic prescription and one set for those who are not. They then liaise with their local centre (the centre responsible for setting up the site) when they have allocated their existing packs to trial participants and reallocation of medication, if deemed necessary, only occurs within the same centre and same subgroup of participants, having delayed antibiotic prescription or not. They also receive an equal number of participant folders containing unique participant trial IDs.

The recruiting clinician allocates the patient one pack of medication from the appropriate set of pre-randomized medications and they record the unique medication ID on the baseline case report form, CRF. The recruiting clinician informs their local study centre (Oxford, Bristol or Southampton) which medication has been allocated to which participant trial ID and the local study centre keeps a log of all allocated medication and participant trial IDs. The recruiting clinician also enters the participant trial ID on the drug allocation log on site against the allocated medication ID.

The trial investigators have reviewed the clinical safety of the study and do not feel that an emergency 24-hour unblinding service is required. The only major adverse event where clinical management might be affected by this knowledge is anaphylaxis, and, as the medication is taken by the participant under observation in the general practice during working hours, this will be managed in hours if required. In addition an independent clinician has confirmed that clinical care offered to a patient presenting with an adverse event or serious adverse event, AE/SAEwould not be influenced by knowledge of which study arm they were in. Participants remain in the practice for 10 minutes after the medication has been taken to ensure that any immediate reaction can be treated. In the very rare event that analysis of the bacterial throat swab reveals an unusual and potentially dangerous pathogen; the Chief Investigator will be contacted to assess the need for emergency unblinding and informing the participant’s practice. This information will only be received, and the practice contactable, in office hours.

A standardized procedure for emergency unblinding is available. The codes will only be broken in case of a major adverse event (such as anaphylaxis or admission to hospital with a life-threatening illness (for example septicemia, meningitis, severe pneumonia requiring ITU admission or death)). The randomization code is stored electronically on a secure password-protected drive and access is restricted to the independent statistician. If unblinding is deemed necessary the Chief Investigator or designated representative will inform the independent statistician to notify the relevant responsible clinician of the treatment allocation for the relevant participant. The trial investigators will not be informed which arm of the trial the participant was allocated to. If randomization of a participant is unblinded during the study then data for that participant, if available, will be included in the intention-to-treat analysis.

The procedures for code break at the end of the trial will be as follows: once all the data queries have been resolved, a blind data review meeting will be initiated involving the trial statistician, the data manager, the trial manager and the Chief Investigator. All protocol violations will be reviewed and a list of study populations for analysis will be generated and signed off by the Chief Investigator and the statistician. At this point, the database will be locked and decoding of the allocation will be allowed.

#### Subsequent assessments

Following the baseline trial assessment participants complete a symptom diary reporting upon the resolution of symptoms and time to onset of pain relief, and rating their pain on a visual analogue scale every day for seven days on paper. As well as recording the severity and duration of their symptoms, this also includes providing information about NHS resource use, out-of-pocket expenditure, use of over-the-counter and prescription medications and time off work and/or education or foregone leisure time. Within the symptom diary we also ask participants to complete the EuroQol EQ-5D-5L instrument [20] daily for seven days following study entry.

Participants are telephoned or texted at 24 and 48 hours to support collection of the primary outcome and secondary outcomes. As preference this contact will be made via text message because of the greater accuracy with times and standardization. They are additionally telephoned in the first 96 hours if required to support and encourage completion of the symptom diary; they will also receive a text message at day four and day nine to encourage completion of the symptom diary and to remind them to return it to the PC-CTU. Follow-up is being undertaken by research coordinators at all three centers. Follow-up continues for seven days from the initial day of recruitment. Participants are asked to report in the diary any use of medications, including whether they obtained and completed the delayed antibiotic prescription. If participants do not complete the symptom diary over the seven days we send them a short questionnaire after this in order to collect information for key secondary outcomes relating to the first four days after taking the trial medication and, if needed, they are telephoned in order to help them complete the questionnaire. All paper diaries and questionnaires are sent back to the respective centre in pre-paid envelopes.

A review of the primary care notes is undertaken by the recruiting primary care site one month post-randomization, to record repeat presentation to a GP, Emergency Department or out–of-hours primary care centre with symptoms or complications of sore throat, hospital admissions and use of prescription medications. Baseline information about past medical history and acute and repeat medication usage is also collected.

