## Methods/Design

### Objectives

The primary objective of the trial is to investigate if, in adults ≥18 years presenting to primary care with acute sore throat, the use of a single dose of oral dexamethasone leads to increased speed of resolution or improvement in symptoms compared with placebo.

The trial has several secondary objectives. Firstly, to investigate whether dexamethasone compared with placebo leads to increased resolution or improvement in symptoms in those patients who have not been prescribed antibiotics. Secondly, to investigate whether dexamethasone compared to placebo will, in those patients offered a delayed antibiotic prescription, reduce the number of patients taking antibiotics for their sore throat within seven days. Thirdly, to investigate whether a single dose of oral dexamethasone compared to placebo will: reduce time away from work or education within seven days, not increase the incidence of hospital admission with complications related to sore throat (such as peritonsillar abscess) within 28 days, not increase repeat attendance at the GP within 28 days with symptoms or complications of sore throat, and be cost-effective. Fourthly, to assess predictors of response to corticosteroids including existing severity scores (FeverPAIN score and Centor score), baseline factors and positive bacterial throat swab.

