### Statistics

#### Statistical analysis for effectiveness and safety

The primary analysis will be intention-to-treat assuming no resolution for missing data. The proportion of complete resolution at 24 hours reported by participants will be compared between two treatment arms using a generalized linear regression model for binary data adjusting for whether participants are prescribed antibiotics or not. The proportion of complete resolution at 24 hours in those participants who have not been prescribed antibiotics (on which this trial is powered) will be compared in the same way.

Logistic regression adjusting for whether participants are prescribed antibiotics or not will also be performed to estimate the differences in the proportions of binary secondary outcomes including reported complete resolution at 48 hours, hospital admission within 28 days, attendance at GP practice, Emergency Departments, or out-of-hours centers within 28 days with symptoms or complications associated with sore throat and uptake of delayed antibiotic prescription within seven days. We will explore whether positive bacterial throat swab, FeverPAIN score, Centor score and other baseline factors predict response to corticosteroid. Use of over-the-counter and prescribed medicine other than antibiotics will be summarized and compared using chi-square tests.

Mean and standard deviations for reported time to onset of pain relief, time to complete resolution of pain, duration of moderately bad symptoms recorded by validated symptom diary and time missed from work or education over the seven days from treatment onset will be calculated and compared between two treatment arms using a linear regression adjusting for antibiotic prescription. We will use data from participants’ diary on throat pain, pain on swallowing and difficulty in swallowing by visual analogue scale within seven days post-randomization to calculate areas under the curves as proxies for a summary measurement and tested for a difference between two arms using a linear regression adjusted for antibiotics prescription. All model assumptions will be assessed and if data do not conform to assumptions the alternatives will be explored. Symptoms of interest will be summarized in the proportions and difference between two treatment arms and 95% CI will be calculated. Full description of the methods to be used will be stated in a trial statistical analysis plan.

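### The back-up questionnaire for participants without a completed diary stops at day 4, although antibiotic uptake and time off work or education are seven-day outcomes

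*Protocol article*

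**What the plan says.** The Objectives section of the protocol article makes it a secondary aim, in patients offered a delayed prescription, to "reduce the number of patients taking antibiotics for their sore throat within seven days". The section on statistical analysis for effectiveness and safety lists "uptake of delayed antibiotic prescription within seven days" among the binary outcomes for logistic regression. Time away from work or education is also defined over seven days, in the Objectives and in the analysis section.

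Under Screening and eligibility assessment, a delayed prescription comes with "instructions for the antibiotics to be collected and used after three to five days if the patient feels their symptoms are not starting to improve". Patients who clearly deteriorate may start earlier.

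Under Subsequent assessments, three sources are described:

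- **Diary, seven days.** Participants report in it "whether they obtained and completed the delayed antibiotic prescription", along with time off work or education.
- **Back-up questionnaire.** "If participants do not complete the symptom diary over the seven days we send them a short questionnaire after this"; its purpose is to "collect information for key secondary outcomes relating to the first four days after taking the trial medication". Telephone help is available to complete it.
- **One-month notes review by the practice.** It records re-presentations, "hospital admissions and use of prescription medications". The Concomitant medication section also names the notes review as an alternative to the diary for recording medication.

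**The concern.** The fallback exists to rescue key secondary outcomes when the diary fails. For two of the seven-day outcomes its window is too short. For antibiotic uptake it also ends in the middle of the period in which patients are told to start, so the uncovered days include part of the time when uptake is most expected.

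The four-day limit is not forced by timing, because the form goes out after all seven days have passed. Nor is it a detail that an article leaves to the analysis plan. The article states the window, and no analysis plan can recover answers to a question that the form never asked.

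At stake is the completeness of the antibiotic-sparing outcome and of the time-off outcome. The primary outcome is collected by text or telephone at 24 hours and is not affected.

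**Working it through.** The article gives no figure for this point to reproduce. The check compares time windows, followed by an illustration on assumed inputs.

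**Windows side by side** (counting the first four days as days 1-4; the article does not say how the questionnaire numbers them)

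| Item | Window | Section |
|---|---|---|
| Antibiotic uptake | to day 7 | Objectives; Statistical analysis |
| Time off work or education | to day 7 | Objectives; Statistical analysis |
| Advised start of delayed antibiotic | after 3 to 5 days, earlier if clearly worse | Screening and eligibility assessment |
| Back-up questionnaire | days 1-4, sent after day 7 | Subsequent assessments |

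Uncovered days: 7 - 4 = 3 (days 5, 6 and 7). Day 5 lies within the advised start period. If the dosing day counts as the first of the four, the window closes a day earlier.

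**What the other sources add on days 5-7**

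- *Diary:* by definition not completed in this group. A partly filled diary may hold some days.
- *Notes review, antibiotics:* it covers prescription medication whether or not a diary came back. However, the delayed script is arranged at the first consultation and is then either handed over at the baseline assessment or left at reception. A notes entry can show that it was issued, and perhaps that it was collected where it was left at reception. The article does not say that the review establishes whether, or on which day, the patient took it. The objective concerns taking.
- *Notes review, time off:* not among the items listed.

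**Illustration of size** (all inputs except 566 are assumptions for this purpose)

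- Participants with a delayed script: 0.5 × 566 = 283. The half is borrowed from the sample-size section's figure for antibiotic prescribing.
- Share without a diary, m: 15% to 20%. These are the sample-size allowances for loss to follow-up, used only as a stand-in. The article gives no diary return rate.
- Participants concerned: 0.15 × 283 = 42 to 0.20 × 283 = 57.
- Share of uptake after day 4, f: 20% to 60%, assumed.
- Share of all uptake unseen = m × f, if the questionnaire is the only source, everyone without a diary returns it, and uptake is equally common with and without a diary.

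| | f = 20% | f = 60% |
|---|---|---|
| m = 15% | 3% | 9% |
| m = 20% | 4% | 12% |

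**The case against.** The strongest reply is that the article does not list the questionnaire's items. One secondary outcome, symptom severity on days two to four after the consultation, fits a four-day form well, so the form may never have been meant to measure uptake. In that case uptake is simply missing when the diary is missing, like any other diary item, and the article already plans to compare missing outcome data between arms. This stands as a caution about wording, but it does not remove the gap. If the form asks about uptake, the answer stops at day 4; if it does not, there is no self-report fallback at all.

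The second reply is the notes review, which does not depend on the diary. This stands in part. A new antibiotic prescription would show in the notes, and collection from reception might. Taking the original script is the weak point, and time off is not covered.

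Third, a reader might infer that late starters will be recorded as non-users and that the result is therefore tilted towards dexamethasone. The documents do not support that. The only imputation rule in the article concerns complete resolution, and nothing codes a four-day responder as a non-user. The tilt would need such coding and, in addition, a treatment effect that moves uptake past day 4.

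Fourth, the illustrative percentages are soft, and this objection stands in full. The loss allowance is not a diary return rate. People who are truly lost return no questionnaire either, so a longer window recovers nothing for them. Patients who worsen may start early and so fall inside the window. Diary return is also supported by a gift card, text reminders and a call.

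**Conclusion.** The point holds as a mismatch of stated windows. For participants without a completed diary, self-reported antibiotic uptake and time off work or education on days 5-7 is not collected, and the notes review is at best a partial substitute for the first and is not said to cover the second.

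The size cannot be derived from the document. The 3% to 12% range shows only what the assumed inputs would imply and should not be quoted as an estimate. It would be too strong to say that uptake in these participants is lost outright, because starts up to day 4 are captured if the form asks about them and the notes review may supply some of the rest. It would also be too strong to claim a bias in a known direction. Bias towards dexamethasone would arise only if treatment postpones uptake beyond day 4 and four-day responders are counted as non-users. The point concerns secondary outcomes in a subset of participants, and it is worth acting on because the remedy is cheap.

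**What to change.** Keep the four-day window for the symptom-severity items. On the same form, and in the call that helps participants complete it, add:

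- whether the delayed antibiotic was started by day 7 and, if so, on which day;
- the number of days off work or education up to day 7.

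State that participants with only four-day information are treated as missing, not as non-users, for days 5-7. If the notes review is meant to supply uptake for participants without a diary, say so and describe how it tells taking from issue.

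The cost is one or two questions on a form already sent after day 7, and a minor amendment. The downside is slightly longer recall and a slightly longer form. The delayed-prescription advice to patients is not touched.
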